### 9.6.1 Male Subjects

The investigator shall use their best efforts in order to ensure that male patients

- inform him/her if their partners get pregnant while the Patient is still treated with the IMP;
- provide him/her the contact details of the healthcare provider who follows the pregnancy in question.

If a female partner of a male subject taking the IMP becomes pregnant, the investigator shall:

- advise that the partner consults her general practitioner or gynecologist as soon as possible;
- (in case romidepsin exposure) provide the information collected to Celgene's Drug Safety Department, using the Pregnancy Reporting Form or an approved equivalent form.

## 9.7 SCIENTIFIC COMMITTEE

A Scientific committee will be formed to review clinical data and stopping rules. The committee will be composed of the coordinating investigator plus two physicians of the investigator team and one external physician. See attachment P for details

## 9.8 EXPEDITED REPORTING OF ADVERSE EVENTS

### 9.8.1 Reporting to Regulatory Authorities and the Ethics Committee

The sponsor will inform the Spanish Medicines Agency (Ministry of Health), the competent authorities of the autonomous region and the Ethics Committees implicated in the clinical trial about any important information of security of the IMPs.

The sponsor will inform the Spanish Medicines Agency (Ministry of Health) of any SUSAR which may be related to the study treatment.

The sponsor will inform competent authorities of the implicated autonomous region of any SUSAR which may be related to the study treatment, and that have been happened in patients in its autonomous region.

The sponsor will inform the Ethics Committee of any SUSAR which may be related to the study treatment, and that have been happened in patients included in its sphere of action.

The Sponsor will inform relevant Regulatory Authorities and Ethics Committees;

- Of all relevant information about SUSAR that are fatal or life-threatening as soon as possible, and in any case no later than 7 days after knowledge of such a case. Relevant follow-up information for these cases will be subsequently be submitted within an additional eight days
- Of all other SUSAR as soon as possible, but within a maximum of 15 days of first knowledge by the investigator.

#### 9.8.2 Immediate reporting by Investigator to Sponsor

The investigator will inform the Sponsor of all SAEs within 24 hours in order that the sponsor can fulfill their regulatory reporting obligations within the required timeframes.

#### 9.8.3 Reporting by Sponsor to Celgene

The Sponsor will supply Celgene with a copy of all SAEs which involve exposure to romidepsin within 24 hours of being made aware of the event regardless of whether or not the event is listed in the reference document (e.g. IB, SmPC).

The Sponsor will provide Celgene with a copy of the annual periodic safety report e.g. Development Update Safety Report (DSUR) at the time of submission to the Regulatory Authority and Ethics Committee.

#### 9.8.4 Reporting by Sponsor to Coordinating investigator

The Sponsor will inform the Coordinating investigator of all SAEs within 24 hours in order that the Coordinating investigator can call the scientific committee to assess trial stopping rules.

## 10 STATISTICS

The primary safety and tolerability analysis will include a description and summary of the number and percentage of grade  $\geq 3$  AE and SAE; their grading and imputability for both MVA.HIVconsV and RMD administrations.

### 10.1 RESPONSE EVALUATION (EFFICACY)

Two main efficacy endpoints will be evaluated in the BCN02-trial as follows:

Part A) Efficacy of the combined intervention (Kick & kill strategy) in the reduction of viral reservoir will be expressed by total HIV-1 DNA copies per million purified CD4+ T cells measured by quantitative digital droplet PCR (ddPCR) at baseline and 1 week after 3rd dose of RMD. Wilcoxon signed rank test will be used for comparisons.

Part B) Efficacy of HIVconsV vaccines in combination with RMD on viral rebound containment after treatment interruption will be evaluated by analysing the proportion of individuals who maintain sustained pVL <2,000 copies/ml at week 29 (12weeks after treatment cessation). Complementary, a survival analysis will be performed to describe time to rebound during the MAP period. Taking into consideration recent published data suggesting that early treatment initiation could favor a delayed viral rebound/spontaneous viral control in 10% in opposition to <5% in chronically-treated individuals, a positive efficacy signal has been established if at least >20% of individuals remain with pVL <2,000 copies/ml at w12 of MAP (pre-defined efficacy threshold).

Regarding virological and immunogenicity endpoints: Differences in the breadth and magnitude of different virological and immune parameters analyses between two longitudinal determinations in the same individuals will be assessed using a Wilcoxon signed-rank test. Correlations between the virologic, immune parameters and clinical outcome will be performed using Pearson test.

Population PK/PD analysis: Briefly, a pharmacokinetic model will be developed using a population approach by means of the software NONMEM 7.3. The population approach allows us, through an intensive modelling exercise, to analyze the data from all participants at the same time but keeping their individual origin. Therefore, estimates for the pharmacokinetic parameters describing not only the mean tendency of the concentration-time course in the population but also at the individual levels will be obtained. The main steps to develop the proposed population pharmacokinetic model are: 1) The pharmacokinetic profile of RMD using the data from the experimental phase of the project will be established: one, two or three compartment models to describe RMD pharmacokinetics will be assessed; 2) Interindividual variability in RMD pharmacokinetic parameters as well as interoccasion variability will be determined, and; 3) The influence of individual characteristics (covariates) in RMD pharmacokinetic parameters will be incorporated into the model. This process will consist of two steps: *forward inclusion* and *backward elimination*. Statistical significance cut-offs for retaining a covariate into the model during the *forward inclusion* and the *backward elimination* steps will be 0.05 and 0.01, respectively. In addition, those covariates without clinical

plausibility will be removed from the model. Once the model had been developed, its predictive capacity will be evaluated by means of simulation and resampling methods (Monte Carlo and bootstrapping, respectively). The final model will be used to evaluate the relationship between RMD exposure and the magnitude of either inhibition of histone deacetylation, HIV reactivation and CTL. Full RMD pharmacokinetic profiles after each RMD dose will be simulated, and area under the curve, maximum and minimum RMD concentrations in plasma will be determined at each occasion and for each participant. A PK/PD analysis will be carried out to evaluate the relationship between each PK parameter and each pharmacodynamic endpoint (lineal, exponential or maximum effects models will be tested). The results from this analysis will be used to determine, through simulation exercises, the dose of RMD to be given to each particular patient to maximize the chances to get the desired effect with minimum risk of deleterious effects.

Correlates of control: By multivariate regression techniques and integration of omics data, biological and clinical markers that predict the effect in the control of viral rebound after the MAP will be analyzed. Both the identification of predictors and the calculation of predictive power of the model will be performed within a process of "internal validation" using resampling techniques (bootstrapping and cross-validation).

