  - 2.5. *In vivo* CTL toxicity assessment based on the most relevant marker from Endpoint 1 (viability, activation, ex) before RMD infusion and after 24 and 72h (RMD1), 12 and 72h (RMD2) and 12, 72 and 7 days (RMD3)
  - 2.6. Development of a population PK/PD analysis to integrate pharmacokinetics of RMD and *in vivo* observed effects of RMD
3. To evaluate the immunogenicity of booster vaccinations with MVA.HIVconsv before and after RMD administration and the effect on viral rebound control after discontinuation of cART.
    - 3.1. To evaluate immunogenicity of booster vaccinations, HIVconsv-specific T cell responses will be measured before, 1, 4 and 8 weeks after both booster vaccinations (MVA1 and MVA2) by IFN $\gamma$  ELISPOT using peptide pools covering different HIV proteins and HIVcons sequences. Total HIVconsv magnitude as well as HIVconsv focus over the rest of HIV-1 specific responses will be compared over time. These results will enable the futility analyses (see section 5.6)
    - 3.2. Evaluation of the effect MVA.HIVconsv boost vaccinations on viral suppressive capacity of CD8+ T cells in vitro, using a flow cytometric assay 4 weeks after MVA2.
    - 3.3. Determine the proportion of individuals who initiate a MAP following the futility analysis
    - 3.4. Determine the proportion of individuals who maintain sustained pVL <2,000 copies/ml during the first 12weeks after treatment cessation.
    - 3.5. Determine the proportion of individuals in whom cART is reinitiated due to viral rebound (2 consecutive pVL >2,000 copies/ml 3-5 days apart), >50% drop in CD4 cell counts, <450 cells/mm^3 and/or symptomatic acute retroviral syndrome.
    - 3.6. Evaluate the emergence of viral resistance during MAP phase
    - 3.7. Evaluate the viral suppression rates 6 months after treatment resumption.

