### 7.3.3 Related to cART interruption

As persistent detectable viral replication may induce immune activation that could favor a faster viral rebound after cART cessation, cART interruption will only be indicated if plasma viral load (pVL) is below the limit of detection in 2 consecutive determinations, spaced at least 1 week, at MAP visit (MVA2+8w). In case that MVA.HIVconsv second booster immunization may induce repetitive detectable plasma HIV-1 RNA determination still present at MAP visit, cART interruption will be postponed until 2 consecutive determinations are achieved.

Any individual for who is being considered for postponement of cART interruption will be discussed with the trial team.

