#### **8.1.14 MAP – Monitored antiretroviral pause and MVA2+8w – Eight weeks post MVA2 vaccination (17 weeks)**

Following procedures will be performed at both clinical sites (HGTIP and HC):

- Blood extraction including:
  - Viral load, biochemistry and hematological parameters.
  - Plasma and PBMC storage following scheme detailed in attachment K
- cART adherence assessment (SERAD questionnaire)
- Clinical visit, adverse event register
- Review acceptability for cART interruption after interim analyses (which will be performed at week 13 and be provided by investigational team in advance and recorded in 'Indication for MAP phase' form, attachment X)
- Review acceptability for cART interruption regarding plasma viral load suppression (pVL below the limit of detection in 2 consecutive determinations, spaced at least 1 week, and recorded in 'Indication for MAP phase' form, attachment X)
- Phase 2 study explanation including: cART interruption, site, weekly clinical visit, qualitative plasma viral load monitoring, criteria for cART resumption.
- CRF data collection

Once analytical results are available, cART interruption will be confirmed telephonically by study physician and first visit in BCN-Checkpoint will be scheduled.

In cases where pVL is not undetectable for 2 consecutive determinations, MAP will be postponed and extra visits will be scheduled (every week if pVL is 20-500 copies/mL, every two weeks if pVL is >500 copies/mL) including the following procedures until acceptability criteria for cART interruption are met.

- Blood extraction including:
  - Viral load, biochemistry and hematological parameters.
  - Plasma and PBMC storage.
- cART adherence assessment (SERAD questionnaire)
- Clinical visit, adverse event register

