### 8.1.15 MAP phase monitoring

Monitoring visits during the MAP phase will be performed at BCN-Checkpoint community center (see flow chart below). A specific MAP Phase Monitoring Form (attachment E) will be used to collect data.

During first 12 weeks post-MAP (from week 18 to week 29):

- Weekly visits will be performed, including:
  - o Clinical visit and adverse events register
  - o Reporting of symptoms suggestive of acute retroviral syndrome (including its severity grade):

|                                                  |                                                 |                                       |
|--------------------------------------------------|-------------------------------------------------|---------------------------------------|
|  Fever of unknown origin |  Headache               |  Pharyngitis  |
|  Lymphadenopathy         |  Transaminase elevation |  Lymphopenia  |
|  Oral candidiasis        |  Myalgia/arthralgia     |  Night sweats |

- |                                           |                                           |                                              |
|-------------------------------------------|-------------------------------------------|----------------------------------------------|
|  Fatigue          |  Nausea, vomiting |  Hepato/splenomegaly |
|  Rash             |  Diarrhea         |  Others              |
|  Trombochytopenia |                                           |                                              |

- 5ml blood extraction for :
  - Qualitative viral load test (Xpert HIV-1 Qual de Cepheid)
- Discussion on treatment resumption: recommendation on cART resumption will be assessed based on clinical visit, willingness of patients to resume treatment and detection of viral load in the qualitative test.
- Schedule of next appointment.
- Visits at 2, 4, 8, and 12 weeks after treatment interruptions (weeks 19, 21, 25 and 29) will also include
  - Biochemistry and hematological parameters, viral load and CD4 count (performed at an external Lab)

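### The Part B control endpoint has conflicting time anchors and does not require participants to be off cART, so a restart before week 12 can be scored as viral control

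*Protocol*

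**What the plan says.** Section 10.1 defines Part B efficacy as the proportion who "maintain sustained pVL <2,000 copies/ml at week 29 (12weeks after treatment cessation"). The next part of that paragraph sets the decision rule: "a positive efficacy signal has been established if at least >20% of individuals remain with pVL <2,000 copies/ml at w12 of MAP". Endpoint 3.4 in section 5.3.2 counts those who "maintain sustained pVL <2,000 copies/ml during the first 12weeks after treatment cessation". Endpoint 3.5 separately counts participants "in whom cART is reinitiated due to viral rebound (2 consecutive pVL >2,000 copies/ml 3-5 days apart), >50% drop in CD4 cell counts", a CD4 count below 450 cells/mm³, or symptomatic acute retroviral syndrome.

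The pause is planned for week 17 (section 5.2). Section 7.3.3 says that, if viral load is still detectable, "cART interruption will be postponed until 2 consecutive determinations are achieved". Section 8.1.14 repeats that "MAP will be postponed and extra visits will be scheduled", and goes on to provide for delay beyond 12 weeks after the second vaccination, which is study week 21. No upper limit is given.

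On restarting, section 8.1.16 joins symptoms, laboratory abnormalities and CD4 falls to the viral load criterion by and/or. Section 8.1.15 says "recommendation on cART resumption will be assessed based on clinical visit, willingness of patients to resume treatment" and, as a further consideration in the same list, detection of virus in the qualitative test.

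**The concern.** Two features of the definition can each raise the observed proportion.

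First, 10.1 treats a study week and a time since cessation as the same point. For anyone whose pause is postponed they differ, and the week-29 reading gives a shorter time off treatment in which to rebound.

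Second, and more important, success is defined on viral load alone. A participant who restarts early with viral load below 2,000 copies/ml, and is then re-suppressed by the drugs, has viral load below 2,000 throughout. That result says nothing about control without treatment. Nothing makes endpoints 3.4 and 3.5 mutually exclusive, so the same person could count as controlled in one and as restarted in the other.

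At stake is the pre-defined efficacy signal. With at most 24 participants, it turns on very few people.

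**Working it through.** **Time anchors.** Planned cessation is week 17, and 17 + 12 = 29, so the two anchors in 10.1 agree for a pause that starts on schedule. In general, time off cART at study week 29 is 29 minus the week of cessation:

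| cART stopped at study week | Weeks off cART at week 29 |
|---|---|
| 17 | 12 |
| 19 | 10 |
| 21 (second vaccination + 12 weeks: 9 + 12) | 8 |
| 25 | 4 |

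The threshold sentence in 10.1 (week 12 of the pause) and endpoint 3.4 give 12 weeks in every row. Only the week-29 label departs from this.

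**Can cART be restarted below 2,000 copies/ml?** Yes. In section 8.1.16 the and/or makes symptoms, laboratory abnormality or CD4 fall sufficient without the viral load criterion. The branch in which cART is not resumed requires both a second value below 2,000 and none of those findings. Endpoint 3.5 also lists CD4 fall and symptoms as restart reasons besides rebound. Neither 3.4 nor 10.1 says how such a participant is scored.

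**Effect on the >20% rule.** The protocol gives no power or error rate for Part B, so there is no figure of its own to reproduce. Inputs:

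- n = 24, the maximum in section 10.3. The number entering the pause is not stated, so n = 20, 15 and 12 are assumptions.
- True control rate 10%, the reference for early-treated individuals in 10.1.
- m = 1 or 2 restarts below 2,000 copies/ml scored as control. This is an assumption.

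The count needed is the smallest integer r above 0.20 × n. For n = 24, 0.20 × 24 = 4.8, so r = 5 (5/24 = 20.8%; 4/24 = 16.7%).

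- No misclassification: P(X ≥ r), with X ~ Binomial(n, 0.10).
- m restarts scored as control: P(Y ≥ r − m), with Y ~ Binomial(n − m, 0.10).

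For n = 24 and m = 1 this is P(Y ≥ 4) with 23 participants; for m = 2 it is P(Y ≥ 3) with 22.

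| n | r | m = 0 | m = 1 | m = 2 |
|---|---|---|---|---|
| 24 | 5 | 0.085 | 0.193 | 0.380 |
| 20 | 5 | 0.043 | 0.115 | 0.266 |
| 15 | 4 | 0.056 | 0.158 | 0.379 |
| 12 | 3 | 0.111 | 0.303 | 0.651 |

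If the same restarts were scored as not controlled, the chance of a signal would be no higher than the m = 0 column.

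**The case against.** The best reply is that the intended meaning is clear. A monitored antiretroviral pause is by name a period off treatment, and remaining below 2,000 at week 12 of it naturally describes someone still in the pause. Under section 8.1.16 a participant who restarts moves to the cART follow-up visits, so has no week-12 pause visit to score. Week numbers elsewhere are nominal: section 8.1.15 pairs weeks 19, 21, 25 and 29 with 2, 4, 8 and 12 weeks after interruption. Part B outcomes are secondary in an uncontrolled pilot, no test is attached to the 20% line, and scoring of restarts could sit in a statistical analysis plan that is not shown.

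Much of this stands, and it rules out three stronger readings.

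- A reader might infer that postponed pauses are counted as control at week 29. The documents do not say so: the same phrase adds 12 weeks after cessation, and the threshold and endpoint 3.4 run from cessation. This is a conflict to reconcile.
- A reader might infer that a 4-week postponement alone takes an ineffective regimen over 20%. That needs a constant rebound hazard and a 12-week time point for the 10% reference, which 10.1 does not give. On those assumptions the 8-week proportion is 0.10^(8/12) = 0.215. The line is then crossed only if 0.10 + 0.115f > 0.20, that is, if a fraction f above 0.87 is postponed (21 of 24).
- A reader might infer that the protocol declares early restarts to be successes, or allows restart on the participant's wish alone. It is silent on the scoring, and section 8.1.15 lists willingness together with the clinical visit and the qualitative test.

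What does not stand is that the point can be left to the analysis plan. The protocol itself fixes the endpoint, time point and threshold, with anchors that disagree and no condition on treatment status.

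**Conclusion.** The point holds as an inconsistency in the time anchor and, more seriously, as an endpoint that is incomplete on treatment status. The wording leans towards participants still in the pause but does not make this a condition, while restart below 2,000 copies/ml is expressly provided for. At a true rate of 10% and n = 24, one or two restarts scored as control raise the chance of a positive signal from 0.085 to 0.193 or 0.380, and the direction is always towards a signal. These figures assume independent participants, a 10% rate in the rest, and that such restarts occur and are scored literally; how many will occur cannot be known from the protocol. No size is claimed for the week-29 conflict.

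**What to change.** - In section 10.1, delete week 29 and read the endpoint 12 weeks after each participant's own date of cART cessation. Endpoint 3.4 already has this anchor.
- In endpoint 3.4 and section 10.1, define success as no cART resumption and no confirmed viral load above 2,000 copies/ml through that date. Score any earlier resumption, for whatever reason, as not controlled.
- Add a sensitivity analysis that treats non-virological restarts differently.
- Reconcile the CD4 levels in the restart criteria: below 450 in endpoint 3.5, below 500 in section 8.1.16.

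The cost is wording in sections 5.3.2 and 10.1. The clinical restart rules are not changed by the scoring rule. The downside is that, compared with the literal reading, requiring participants to be off cART can only leave the reported proportion the same or lower it, and a participant who restarts for a non-virological reason counts as a failure; the sensitivity analysis shows how much that matters. The handling of restarts in the time-to-rebound analysis is a separate choice on which statisticians differ, and no change is asked for there.

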## 3.1 HYPOTHESIS

1. Administration of RMD (5 mg/m^2) to early-suppressed HIV infected individuals and whose CTL response has been refocused to more conserved regions of HIV by HIVconsv therapeutic vaccines will be safe and will reduce the viral reservoir.
2. Both HIV reactivation as well as, in case it is confirmed, eventual toxicity on CTL functionality by RMD, will be related to the exposure to RMD, allowing the definition of a RMD therapeutic range in this specific scenario.
3. After RMD administration, efficient re-stimulation of the cytotoxic response will be reached by MVA.HIVconsv, and the immunogenic response will be associated to the level of immune control after a monitored antiretroviral pause.

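### The protocol fixes Pearson correlation, with no scale or rank alternative, for virological and immune measures and clinical outcome in at most 24 people; it is a weak choice for inverse associations on skewed data and cannot handle censored rebound times.

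*Protocol*

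**What the plan says.** Section 10.1, in the paragraph on virological and immunogenicity endpoints, fixes the correlation method: "Correlations between the virologic, immune parameters and clinical outcome will be performed using Pearson test". It does not say whether values are raw or logged, and it gives no fallback.

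The sentence just before it deals with changes in virological and immune parameters, which "will be assessed using a Wilcoxon signed-rank test". Part A of 10.1 does the same for HIV-1 DNA copies per million CD4+ T cells: "Wilcoxon signed rank test will be used for comparisons".

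The rebound outcomes take two forms:
- **Yes/no.** Section 5.3.2, endpoint 3.4: "Determine the proportion of individuals who maintain sustained pVL <2,000 copies/ml during the first 12weeks after treatment cessation".
- **Time to event.** Section 10.1: "Complementary, a survival analysis will be performed to describe time to rebound during the MAP period".

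Hypothesis 3 in section 3.1 expects that "the immunogenic response will be associated to the level of immune control after a monitored antiretroviral pause".

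Two other parts of 10.1 cover related questions by other methods. Predictors of control after the treatment pause go to multivariate regression with bootstrapping and cross-validation. Romidepsin exposure-effect relations go to PK/PD models.

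**The concern.** Copies per million cells, cell-associated RNA, viral load and ELISPOT counts are the kind of measure that is often right-skewed. The protocol uses rank tests for paired changes in such measures, then a moment-based coefficient for their correlations, in a sample where one or two extreme values can dominate it.

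Direction matters. Some pairs of interest would naturally be inverse, for example a larger reservoir with a shorter time to rebound, or a stronger T-cell response with lower viraemia. On raw right-skewed scales an inverse relation bends into an L-shape that a straight-line coefficient captures poorly.

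The term clinical outcome also takes in a time to rebound that is censored in anyone who does not rebound. These are the participants the trial most hopes to see, and Pearson has no means of marking them as censored.

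At stake is a false finding of no association in a small cohort. Section 7.3.7 says participants cannot be replaced.

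**Working it through.** **No figure to reproduce.** The protocol gives no power, alpha or effect size for these correlations. Section 10.3 gives a maximum of 24 participants and calls the trial a pilot able to detect only a large effect.

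**Assumptions, not in the protocol.** Bivariate lognormal pairs; natural-log SD 0.7, 1.0 or 1.5 in both variables; log-scale correlation ±0.5; two-sided 0.05; t-test on r. Power is by Monte Carlo simulation; a repeat with 40,000 replicates per setting agreed within about one percentage point.

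**Why direction matters.** For lognormal pairs with log-scale SD s and log-scale correlation ρ, the raw-scale correlation is (exp(ρs²) − 1) / (exp(s²) − 1).
- s = 1.0, ρ = −0.5: (0.6065 − 1) / (2.7183 − 1) = −0.23.
- s = 1.0, ρ = +0.5: (1.6487 − 1) / 1.7183 = +0.38.
- s = 1.5, ρ = −0.5: (0.3247 − 1) / (9.4877 − 1) = −0.08.
- s = 1.5, ρ = +0.5: (3.0802 − 1) / 8.4877 = +0.25.

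The same log-scale strength shrinks much more when it is inverse.

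**Power at n = 24, |ρ| = 0.5**

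| Natural-log SD | Raw Pearson, inverse | Raw Pearson, positive | Spearman | Pearson on logs |
|---|---|---|---|---|
| 0.7 | 49% | 59% | 67% | 73% |
| 1.0 | 23% | 51% | 67% | 73% |
| 1.5 | 4% | 42% | 67% | 73% |

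Spearman and log-scale Pearson do not depend on the SD or the direction. Fisher-z check of the last column: atanh(0.5) × √21 − 1.96 = 0.5493 × 4.583 − 1.96 = 0.557, and Φ(0.557) = 0.71.

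**Smaller sample.** At n = 15 (an assumed lower case) and ρ = −0.5, raw Pearson has 27%, 7% and 2% power at log10 SD 0.3, 0.5 and 0.7, against 44% for Spearman. Multiplied by 2.303, these are natural-log SDs of 0.69, 1.15 and 1.61.

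**Type I error.** For continuous pairs, raw Pearson stays at about 5–6% at n = 24.

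**Yes/no control.** Pearson with a binary variable is the point-biserial correlation, equivalent to the equal-variance t-test. The efficacy threshold in 10.1 is more than 20%. Since 0.20 × 24 = 4.8, that means at least 5 of 24. With 5 controllers and log10 SD 0.5–0.7:
- No difference: type I error 5%.
- Marker 1.5 SD higher in controllers: 78–81%, against 78–79% for ranks.
- Marker 1.5 SD lower in controllers: 3–13%, against 79% for ranks.

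With 3 of 24 controllers, type I error is 6.6–7.6%. Power for a lower marker is 0.1–1.6%, against 59–61% for ranks.

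**Time to rebound.** Assumed median 3–4 weeks, capped at 12 weeks (4–18% capped), n = 24, ρ = −0.5: raw Pearson 34–41%, Spearman 66–67%. Log-scale Pearson still reaches 70–73%, so in this setting most of the power loss comes from skew. The censoring problem is separate: both coefficients enter the capped value as an observed time.

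**The case against.** The case against has force on several points.

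- **Not every association is left to Pearson.** A reader might infer that it is, and that Hypothesis 3 rests on this test. The documents do not support that. The correlates-of-control analysis is the dedicated study of what predicts control after the pause, and it uses multivariate regression. Time to rebound has its own survival analysis, although that is planned only as description. The Pearson sentence is a bivariate supplement, yet it still names clinical outcome.
- **Skew does not always cost most of the power.** For positive associations the loss is moderate, and for inverse ones with mild skew it is about a quarter (49% against 67%). A stronger response going with longer control would be a positive pair, so the inverse case is not the rule.
- **Yes/no outcomes are not out of reach.** Pearson is computable there and works when controllers have the higher marker values.
- **Skew and detection limits are not documented.** The protocol gives no spread for any assay. Section 3 reports that reservoir measurements in the source cohort were detectable in everyone one year after starting treatment.
- **Scale might be set in a statistical analysis plan.** On logged values Pearson beats Spearman, so Pearson itself is not the error.

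All of this narrows the point but does not remove it. The protocol makes a positive choice of test with no scale attached, next to rank tests for the same kinds of measure. No transformation makes Pearson suitable for a censored time.

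**Conclusion.** The point holds in limited form. Section 10.1 fixes Pearson without a scale or rank alternative, and applies it to a clinical outcome that includes a right-censored time.

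If the measures are analysed raw and are clearly right-skewed, power for inverse associations at n = 24 falls from about 67% with Spearman to between 49% and 4%, depending on spread. For positive associations it falls to between 59% and 42%. These sizes rest on assumed lognormal data and a log-scale correlation of 0.5, not on figures in the protocol. False positives are not the main concern: the rate is near nominal for continuous pairs and only mildly raised with very few controllers.

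The failure to handle censoring does not depend on those assumptions. It applies whenever a participant does not rebound.

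These are secondary, exploratory correlations. The primary safety and reservoir analyses, the multivariate correlates-of-control analysis and the PK/PD models stand as they are. The change should be made, but the trial's main conclusions do not depend on it.

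**What to change.** Replace the Pearson sentence in section 10.1 with a method for each type of pair:

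- **Continuous pairs** (virological and immune measures): Spearman correlation, or Pearson on log-transformed values, with a 95% confidence interval. Choose one before the data are seen.
- **Control yes/no:** rank-sum test or exact logistic regression.
- **Time to rebound:** Cox regression or a rank concordance measure, with participants who do not rebound censored.

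Add a line saying that these bivariate results support the multivariate correlates-of-control analysis and do not replace it. The cost is a short edit to one paragraph, with no extra samples, visits or participants. Fixing the scale in advance also prevents choosing it after the results are known.
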